**AIM 1: CONDUCT FORMATIVE RESEARCH TO IDENTITY KEY MODIFICATIONS TO 3MV INTERVENTION MANUAL AND IMPLEMENTATION PROTOCOL**

**3.5 FORMATIVE PHASE.** The ultimate objective of Aim 1 is to adapt the 3MV intervention to the OFOV intervention. A schematic overview of the formative phase of Aim 1 is depicted in **Figure 2.**

[figure not shown]
**3.5.1 Step 1 (Assess):** We will conduct focus group discussions (**FGDs**) with parents and authority figures of HBC families to inform the adaptation of the 3MV interventions by deepening our understanding of the range assets in the external (i.e., support, empowerment, boundaries/expectations and constructive use of time) and internal (i.e., positive identity, positive values, social competencies and commitment to learning) domains. The focus groups will also explore their observations of the various stigmas and hardships faced by family members, how these stigmas intersect, and their views on what are best combinations of assets to buffer against the negative effects of intersectional stigma on HIV testing, PrEP use, linkage to care and ARV use. FGDs were chosen because of their suitability for sexual health studies^83,94-96^ and to also capitalize on the type of spontaneous conversation interactions that occur. Re-creating the social dynamics among parents and authority figures is critical to understanding possibilities for assets-building within the social organization of HBC families

We will qualitatively:

1. Characterize the external and internal assets that exist within families, including patterns of commonalities and differences between families.
2. Identify sources of exposures to intersectional stigma among HBC family members.
3. Explore the various ways that intersectional stigma influences health goals in HBC families.
4. Explore content for inclusion in video booster sessions to amplify post-*OFOV* knowledge and skills and counteract intersectional stigma to facilitate the primary study outcomes (see Figure 1).

The data generated in this step will inform how HBC family dynamics, social realities, and assets are addressed in the *OFOV* intervention components.

**3.5.1A Sample Size and Sampling Strategy**. We will conduct 6 FGDs with parents of HBC families. We anticipate that 6-8 parents or parental authority figures will participate in each focus group. Thus, the estimated sample size is between 24-48 parents. Based on our many years of experience working within the house ball community and our geographic concentration in the New York City metro area (inclusive of northern New Jersey and southern Connecticut), we do not expect a wide variation in responses between the focus groups; therefore, we expect that we will reach data saturation by the fourth focus group. Nonetheless, we are prepared to conduct more FGDs if our qualitative analysis reveals that new codes are still emerging even after completing 6 FGDs.

We will conduct a chain-referral method to recruit the sample via **The** **Federation**, ***HLM*** and **The Coalition** (our HBC gCBO partners). Chain-referral was chosen based on the efficiency of tapping into an existing extensive network in which trusted relationships with our community partners can facilitate interest in participating in the study. This process involves recruiting parents who are known to **The Federation, HLM**, and **The Coalition**. They will be asked to invite other parents (whom they consider to be their peers) from their social network to participate in a focus group, as well as members of their families whom they deem authority figures to their house children. As described in section 3.4.4 above, this team has a successful history of recruitment in the HBC. Although we are not employing a purposive sampling strategy, we are conscious of the insidiousness of transphobia; therefore, we will monitor patterns of the participation of transgender-identified individuals and may target recruitment to transgender individuals if we find that they are under-represented in the focus groups.

**3.5.1B. Inclusion criteria for current HBC members**. Individuals are eligible to participate in the FGDs if they are at least 18 years old, are the publicly recognized parents or authority-figures of an HBC family, and their immediate house family-unit has at least twelve members. Individuals will be excluded if:

- Their HBC family has been established for less than 12 months
- The individual lives outside of the New York City metropolitan area

**3.5.1C Data Collection.** FGDs will be conducted by trained research staff from SUNY Downstate who have prior experience in qualitative research methods within Black LGBT communities. We make efforts to employ individuals from the HBC as a community capacity-building and investment tactic. All qualitative data will be digitally recorded and transcribed verbatim. The research project staff will be responsible for the transcription. All transcripts will be verified by two research project staff. After interviews are transcribed and verified for accuracy, recordings will be encrypted and uploaded to a secure cloud-based server at SUNY Downstate.

**3.5.1D Data Analysis**. We will conduct qualitative content analysis, a procedural approach in which data are categorized and reviewed iteratively to generate conclusions based on both explicit and implicit meaning in the text.^97^ We will use NVivo to manage the qualitative data. [name] and [name] will lead the qualitative analysis with assistance from **[name]** and **[name].** [name] will not have any direct access to the qualitative data. During the preparation phase, **[name]** and **[name]** will read the FGD transcripts independently several times to become immersed in the data. Open coding will be used to identify nodes. Open coding will continue until no new nodes are identified. Through an iterative approach, node groups will then be formulated into meaningful categories and sub-categories. Quotes that represent the various categories and sub-categories will be selected and used to illustrate the content of the FGDs. Findings will be discussed among all the investigators and HBC gCBO partners to ensure a balanced and accurate representation of assets and stigmas and how these findings can best be represented and addressed through activities in the adapted intervention. We will also use the guide in the development of storylines and scripts for the video booster sessions will be directed/produced by **[name]** and co-produced by **[name]**. [name] will not have any direct access to project data.

**3.5.2 Step 2 (Decide).** Guided by the formative research results, the team will meet to discuss what specific intervention activities should be modified to incorporate family-based assets. We will conduct an updated scoping review of research literature to identify innovative evidence-based options to enhance focus on assets to facilitate resilience, with special attention to technology and social media options. This will include a review of the current intervention activities and discussion of how they can be refined to include identifying and building assets against intersectional stigma and hardships. In consultation with **The Federation, HLM** and **The Coalition**, we will incorporate changes into the curriculum, identify gaps/errors in logic and make corrections in preparation to conduct a workshop of the intervention with a reference group of HBC families.

**3.5.3 Step 3 (Administer):** After initial modifications, we will conduct a facilitated simulation workshop of the *Our Family Our Voices* intervention activities with two HBC families who previously received the original 3MV. We will conduct separate workshops (versus one joint workshop) because it is consistent with the concept that the intervention is targeted to the family-level and we want to get feedback on its performance within a dynamic that is closest to the one we expect to target in the pilot RCT phase. We will produce a preliminary revised version of the original intervention manual before the workshop and conduct a series of facilitated simulation exercises with role-play over a 3-day period. Participants will work through each of the intervention components, focusing on the family asset-building content and reviewing our approach to “connecting the dots” that these assets are socioecological resources that can buffer against the negative impact of intersectional stigma.

**3.5.4. Step 4 (Produce):** Based on the feedback from the simulation workshop participants and our observations of their engagement with the activities, we will determine what content and approaches to incorporate into the *OFOV* intervention manual and which ones to edit or forego. This includes making final decisions regarding the final storylines and messages for the video boosters. **[name]** (co-investigator) is an expert in the development of video vignettes for use as components of HIV-related intervention with MSM. ^98-100^**[name]** will work with **[name]** and **[name]** on the development and production of vignettes as brief stand-alone videos for viewing every 6-weeks (weeks 6, 12, 18, 24) between 3- and 6-month follow-up. We will give priority consideration to retaining components that have the highest consistency with scientific evidence on HIV risk-reduction and asset-building as well as HBC cultural relevance based on input of **HBC gCBO** partners.

**3.5.5 Step 5 (Topic):** We will engage topic experts to review the adapted manual and provide feedback on its congruence with the original intervention and local sociocultural relevance. A copy of the adapted intervention manual will be provided to **[name]** (co-investigator) is the world’s foremost authority on House Ball culture and factors that influence HIV prevention and care—will review the manual to ensure that it has resonance with ballroom and to avoid contrived product that does not elicit natural authentic connection with members of the HBC. **[name], [name]** and **[name]** (consultants) will review the intervention for cultural resonance as well as to ensure that it maintains fidelity to internal logic of the 3MV intervention on which it is based. [name] and [name] role as paid community consultants is essential to inform the acceptability of the intervention with the focus population but will not have direct contact with collected data. **Our gCBO** partners will give feedback that is key to the local cultural relevance and implementation of OFOV. Letters of support from the topic experts and HBC gCBO partners are included.

**3.5.6 Steps 6 (Integrate) and 7 (Train):** In this step, we will take feedback provided by the topic experts and summarize it in a report that will be distributed to the entire investigative team, including our key collaborators. We will discuss the feedback and provide follow-up clarifying questions to the topic experts, as necessary, before making final revisions to the adapted intervention manual. We will also produce a training manual to standardize training and permit future replication of the intervention in other settings (e.g., HBC families living in southern of United States). We will provide comprehensive training to facilitators whose roles are dedicated to delivering the intervention **(see 3.6.7A, Training of Interventionists)**. We will develop the training to be multi-faceted to facilitate comprehension and retention of training concepts, using strategies that Drs. [name] and [name]^101^ have successfully deployed in other HIV prevention research projects. This will include conducting a joint (including with representatives from **The Federation, HLM,** and **The Coalition**), dry-run rehearsal of the protocol prior to implementation in the pilot CRCT with HBC families.

**AIM 2: DETERMINE THE FEASIBILITY AND ACCEPTABILITY OF THE MODIFIED INTERVENTION**

**MANUAL AND TRIAL PROTOCOL**

**3.6 RANDOMIZED CONTROLLED TRIAL PHASE**. An overview of the RCT phase of is depicted in **Figure 2.**

**3.6.1 Step 8 (Test).**

**Overview of Trial Design.** Using a cluster RCT, we will evaluate the feasibility and preliminary efficacy of *OFOV* compared to waitlist standard of care (SOC) control on uptake of HIV testing and PrEP use (for HIV-negative individuals) and linkage to care and current ARV uptake (for PLHIV) among 6 New York City HBC families over a 6-month period. SOC is defined as the currently available suite of prevention and care services in the NYC metropolitan area. The SOC control will not receive a group/family-based behavioral risk-reduction intervention. Since the HBC is relatively small and recruitment is limited to the NYC metropolitan area, we propose a cluster-randomized design to reduce the likelihood of contamination across families in the HBC. A limitation of randomizing by clusters is a loss of efficiency; thus, the samples size needed to obtain precision in a cluster-randomized trial is usually larger than when randomizing individual participants. Once a cluster is randomized to the treatment condition, it will remain in the assigned condition for the duration of the study. Using this study design, each cluster (family) in the experimental arm will receive both the OFOV intervention over a 2.5-day weekend retreat and video booster sessions every 6-weeks thereafter until the 6-month data collection point. Families in the experimental arm will be asked to follow-up for HIV testing and PrEP services (for HIV negative or status-unknown individuals) or linkage to treatment services (for PLHIV).

Our working hypotheses are that the *OFOV* intervention will increase uptake of HIV testing and PrEP use (for HIV-negative family members) and linkage to care and treatment engagement (for PLHIV who were not in care at baseline). We will measure frequency of HIV testing at 3- and 6-months post-intervention using a combination of online self-report survey and verification by through clinic medical records. We will seek to obtain medical records releases from participants to obtain data on HIV testing, PrEP prescription, engagement in care and ARV use. Our secondary hypotheses are that *OFOV* will increase the number of family-based assets, resilience and reduce number of sex partners and frequency of CAI for members who are not in mutually monogamous relationship with an HIV-negative or virally suppressed partner. We also measure intersectional stigma and asset-impact indicators at all time points (to characterize these in our sample) ^102,103^ Families in the waitlist SOC control arm have the option to participate in OFOV after 6-month data collection.

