The HBC population size is estimated to be approximately 8,000 nationwide, with the largest concentration in New York City.^39^ Despite the emerging visibility and celebration of the HBC’s contributions to culture in the Black LGBT communities; alarming disparities in HIV persist. Previous studies with HBCs identified HIV prevalence as high as 20%^40^ as well as high prevalence of stigma and stressful life events.^40,41^ Moreover, Black HBC members were more likely than non-Black Latinx members to be unaware of their HIV status (83% vs. 33%, p<.001).^41^

**To optimize HIV prevention outcomes for Black MSM, we must go beyond identifying and reducing risk factors towards simultaneously identifying and increasing assets** that are present in their lives. Although we don’t have data on assets among Black LGBT youth, the currently available evidence indicates that, in general, LGBT youth have fewer assets than heterosexual youth. In a population-based survey^21^ of assets among youth in grades 6-12, LGBT youth reported fewer assets than non-LGBT youth in the four family centered domains (see Table 1). The one exception was in the domain of “Constructive use of time”, wherein a greater percentage of LGBT youth reported being engaged in creative activities. Although the data in Table 1 do not show comparisons by race, there is already a substantial literature indicating that LGBT youth of color have worse outcomes compared to the general population of LGBT youth.^42-44^

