**3.6.4C Primary and Secondary Outcomes.** Our primary outcomes will be HIV testing and PrEP use (for HIV-negative or unknown members) or “In HIV care” and “currently on HIV treatment” (for PLHIV) within 6 months of randomization. For HIV-negative MSM we will also record the frequency of HIV testing over the prior 3-months, but we anticipate that few participants will take >1 test in this short period of time. A detailed summary of primary outcome measures is included in Table 3. Our secondary outcomes (see also Table 4) will be number of family-based assets, resilience, number of sexual partners, and relative frequency of CAI. We will also assess sense of community^105^ at all time-points. In our previous research with Black MSM we found that sense of community was associated with increased condom use for anal intercourse (*OR*=1.26, 95%CI 1.05,1.52; p<.05).^14^

**3.6.4D Implementation Outcomes.** We will assess feasibility and acceptability of *OFOV* using a combination of process measures (e.g., intervention completion rate) and validated scales (e.g., peer support evaluation inventory). Implementation outcomes measures are also summarized in Table 4.

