**3.6.5 Data Analysis.** The intervention outcomes will be assessed using a rigorous intention-to-treat (ITT) approach where participants are included in the analysis as originally assigned, regardless of whether they actually receive the intervention or usual care.^111^ First, we will compare baseline data to see if randomization resulted in equivalent groups. If we determine non-equivalence, then the non-equivalent variables will be accounted for in the final analyses using a difference in differences analytic technique where randomization is used to minimize any perception of bias in selection of families by investigators. We will determine the proportions of HIV testing at 3- and 6-month of follow-up assessments among family members with 95% confidence intervals (CI). To test the primary study hypotheses that the intervention will increase uptake of HIV testing (for HIV negative members) and attendance at medical care appointment and ARV use (among PLHIV) within six months of randomization, we will use an uncorrected chi-square statistic, followed by effect size calculation with relative risk (RR). As odds ratio (OR) may overestimate RR for common events like in our study, we will use a modified Poisson approach to estimate RR of intervention relative to SOC and CI by using robust error variances.^112^ Additionally, a modified Poisson regression approach will also be used to compute the RR and 95% CI for the binary outcomes (yes/no) – HIV testing, PrEP use, “engaged in HIV care” and “on ARV treatment”. These outcomes can be dependent on the health care facility (HCF) environment, such that participants at the same HCF may be corrected or “clustered”. To account for the potential post-randomization clustering effect in this CRCT, a generalized linear mixed effects model with a logit link function will be fitted, and this model includes both HCF cluster-level and family-level factors. **See Human Subjects section 4.4. for Power Calculations.**

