The likelihood of intervention contamination across the study groups could not be excluded, because some participants may not receive the respective interventions to which they are randomized, e.g., some members of the control group may end up in situations in which they receive some level of support from a HBC family in the intervention group. Therefore, we will also perform per-protocol analysis, which includes only those participants who strictly adhered to the protocol and report the results along with the results of the ITT analyses.

| **Table 4. Summary of RCT Phase Measures** | |
| --- | --- |
| **Construct** | **Sample Items and reliability** |
| **HIV Testing** (self-report and medical record verified) | Number of HIV tests in past 3-months |
| **PrEP Use** (self-report and medical record verified) | Is participant currently on antiretrovirals for HIV PrEP? |
| **In HIV Care** (self-report and medical record verified) | Has participant attended HIV medical appointment in past 3-months |
| **On HIV Treatment** (self-report and medical record) | Is participant currently on antiretrovirals for HIV treatment? |
| **Condomless anal intercourse** (past 3 months) | Relative frequency = # times condoms used during anal sex / total # episodes of anal sex |
| **Number of sexual partners** | Total number of sexual partners in the past 3 months |
| **Sense of Community Scale^105^** (8-items) | I feel like I am a member of my house family (α=0.87 - 0.92) |
| **Brief Resilience Scale^106^** (6-items) | I tend to bounce back quickly after hard times? (α=0.80-0.91) |
| **READY Tool** (24-items)^102,103^ | My family expects me to try my best. I ask my family questions to get ideas. (α=0.85) |
| **Asset Inventory (40-items)^21^** | I seek advice and counsel from my parents. My family has clear rules and consequences. |
| **Intersectional Stigma (Latent Variable)** |  |
| **HIV Stigma Scale^107^** | |
| *Enacted subscale (10-items)* | Has a healthcare worker not wanted to touch you because you have HIV? (α=0.92) |
| *Vicarious subscale (10-items)* | How often have you heard stories about someone with HIV being refused care? (α=0.88) |
| *Perceived subscale (10-items)* | In your community, how many people think a person with HIV is disgusting? (α=0.94) |
| *Internalized subscale (10-items)* | How often do you feel guilty about having HIV? (α=0.83) |

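### The care and treatment hypothesis concerns PLHIV not in care at baseline, but the primary outcomes and analysis take in all PLHIV, so the estimated effect belongs to a different population

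*Protocol*

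**What the plan says.** Section 3.6.1 gives two populations. The design overview speaks of "linkage to care and current ARV uptake (for PLHIV" with no further condition. The working hypotheses a paragraph later are narrower: "linkage to care and treatment engagement (for PLHIV who were not in care at baseline".

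The sections that carry the analysis use the wider group. Section 3.4.1 names care engagement and current ARV treatment as primary outcomes for PLHIV. Section 3.6.4C sets the primary outcomes "for PLHIV) within 6 months of randomization". Section 3.6.5 says it tests the primary hypotheses, and restates them as "attendance at medical care appointment and ARV use (among PLHIV) within six months of randomization, we will use an uncorrected chi-square statistic".

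Table 4 scores being in HIV care by the item "Has participant attended HIV medical appointment in past 3-months", and being on treatment by whether the participant is on ARVs now. Neither item asks whether this is new since baseline.

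No section shown restricts, stratifies or adjusts the PLHIV outcomes by care status at baseline. Section 3.6.5 brings in difference-in-differences only if the arms turn out unequal at baseline.

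**The concern.** The hypothesis and the test name different people. Linkage can only happen in someone who is not yet linked. A member who is in care and on ARVs at enrolment will often score yes on both Table 4 items in either arm, whatever OFOV does for linkage.

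An analyst who follows section 3.6.5 therefore estimates a mixture: linkage in those out of care, and retention in those already in care. The weights are set by whatever mix of members the six families bring.

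The protocol wants a first effect-size estimate (3.4.1) and will use the pilot to settle the protocol of a full cluster trial (3.7). A mixture read as a linkage effect would misinform that design.

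**Working it through.** **Number of PLHIV.** The protocol states neither an expected number of PLHIV nor a share out of care. Its inputs are n = 100 in six families (3.6.2A) and, from 3.1, "Previous studies with HBCs identified HIV prevalence as high as 20" percent.

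- All PLHIV: 100 x 0.20 = 20, or about 10 per arm.
- Binomial 95% range, ignoring clustering: about 12 to 28.
- With only the minimum of 12 members in each of six families: 72 x 0.20 = 14.4.
- Not in care at baseline, for an assumed share q: 20 x 0.15 = 3; 20 x 0.30 = 6; 20 x 0.50 = 10.

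The value of q is an assumption. The 20% is quoted as a high figure from earlier studies, and the trial's own share may differ.

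**Dilution.** Assumed, not in the protocol: linkage of 30% (control) v 60% (OFOV) in those not in care; 90% with a visit in the past 3 months in those already in care, the same in both arms.

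In the hypothesis population: RR = 0.60 / 0.30 = 2.0 and risk difference = 0.30.

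In all PLHIV, the rate in an arm = (1 - q) x 0.90 + q x linkage rate:

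| q | Control | OFOV | Difference | RR |
| --- | --- | --- | --- | --- |
| 15% | 0.765 + 0.045 = 0.810 | 0.765 + 0.090 = 0.855 | 0.045 | 1.06 |
| 30% | 0.630 + 0.090 = 0.720 | 0.630 + 0.180 = 0.810 | 0.090 | 1.13 |
| 50% | 0.450 + 0.150 = 0.600 | 0.450 + 0.300 = 0.750 | 0.150 | 1.25 |

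The risk difference is q x 0.30 throughout. If attendance in those already in care is 100% instead of 90%, the RRs are 1.05, 1.11 and 1.23.

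**Consequence for a later trial.** At two-sided 0.05 and 80% power, before any cluster inflation:

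- 30% v 60% needs 42 per arm not in care. At q = 30% that means enrolling 42 / 0.30 = 140 PLHIV per arm.
- 72% v 81% in all PLHIV needs 348 per arm.

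**If retention also improves.** At q = 30%, suppose attendance in those already in care rises from 90% to 100% under OFOV. The OFOV rate is 0.70 x 1.00 + 0.30 x 0.60 = 0.88, and RR = 0.88 / 0.72 = 1.22. Part of the effect returns, but the figure now blends retention with linkage.

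**The case against.** The strongest reply is that engagement among all PLHIV is a sensible aim for a status-neutral intervention, and that members already in care can still improve. Both points stand. The care item depends on a visit in the past 3 months, so it can move in either direction, and section 3.4.4C reports better appointment show rates in the earlier PLHIV pilot. It would be wrong to say that these members cannot improve, and the dilution is exact only if retention is unchanged. Rewording the hypothesis to all PLHIV would also remove the contradiction, but the result would then have to be described as engagement and shown by baseline care status.

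Three stronger readings are tempting, and the protocol does not support them.

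- A reader might infer that small counts make the chi-square p-value invalid. At 10 per arm, exact enumeration that ignores clustering puts the true size of a nominal 0.05 test at 0.030 when 80% are in care, and at no more than 0.042 at any rate. Low power alone is not an error in a pilot either, and section 3.6.5 adds modified Poisson and mixed models.
- A reader might apply "to be unaware of their HIV status (83% vs. 33%, p<.001" to the 20 expected PLHIV and conclude that only 20 x (1 - 0.83) = 3.4 would be known. The protocol gives no HIV-positive denominator for that percentage, so it cannot be used this way. As written, the test would use all PLHIV.
- A reader might infer that status groups are formed at follow-up and so break the randomised comparison. No section says that. Including members of unknown status in the testing outcome fits a classification made before testing. The protocol simply does not state the time point.

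**Conclusion.** The contradiction is on the face of the protocol. Section 3.6.1 limits the care and treatment hypothesis to PLHIV not in care at baseline; sections 3.4.1, 3.6.4C and 3.6.5 and Table 4 do not. Followed as written, the plan yields an effect size for another population than the one hypothesised.

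Under the illustrative inputs, a linkage RR of 2.0 would appear as 1.06 to 1.25 for a not-in-care share of 15% to 50%. The size rests on assumed linkage rates, assumed attendance and an assumed share, none of which the protocol gives. The direction holds unless OFOV also improves retention in those already in care. The finding does not depend on the small numbers, but they limit what any test of these outcomes can show.

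**What to change.** Change the wording in 3.6.1, 3.6.4C and 3.6.5 so that hypothesis, outcome and analysis name the same people:

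- Classify HIV status, care status and ARV status at baseline, and keep each member in that group throughout.
- Evaluate linkage in PLHIV not in care at baseline, and ARV start in PLHIV not on ARVs at baseline.
- Report retention in those already in care separately.
- Report these outcomes as counts by arm and family with intervals, without relying on a significance test, and state the number expected in each group.

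The baseline survey and the medical-record release in 3.6.4A, which covers the last HIV visit and the last ARV prescription, give a basis for the classification, so the cost is mainly wording. The downside is that the PLHIV outcomes become openly descriptive.
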